#### Overview of study

For an overview of instruments, order of assessment and moment of assessment see Fig. 1 and Table 1. The first test day takes approximately 4 h, the fifth and tenth test day take three hours and all the other assessments take 45 min. After three, six and 12 m a 30-min telephone follow-up interview will be held.

**Fig. 1 Fig1:**
[figure not shown]
Overview of the measures taken on different test days. Sample characteristics (age, handedness, educational level, medication use, WAIS digit span, NLV, MINI, substance use during life, alcohol use history), neurocognitive tasks (GNGT, AAT, DDT, SWMT, SST, IDED), questionnaires (AUDIT, AASE, BDI, BIS, UPPS, BIS/BAS, STAISTATE, PANAS), extensive craving assessment (AUQ, OCDS, VAS), brief craving assessment (VAS). All these measures will be explained in more detail in the *outcomes and instruments* section. Symbols: X = week before first rTMS session, XX = week after last rTMS session

**Table 1 Tab1:** Overview of measurement instruments and moment of assessment during study. Symbols: X = MR session week before first rTMS session, XX = MR session week after last rTMS session, XXX = three months after last rTMS session, XXXX = six months after last rTMS session, XXXXX = twelve months after last rTMS session

Test day	X	1	2	3	4	5	6	7	8	9	10	XX	XXX	XXXX	XXXXX
WAIS		•													
NLV		•													
MATE-Q		•													
MINI		•													
Alcohol use history		•													
TLFB													•	•	•
VAS		•	•	•	•	•	•	•	•	•	•		•	•	•
AUQ		•				•					•		•	•	•
OCDS		•				•					•		•	•	•
DDT		•				•					•				
Go/No-go		•				•					•				
SST		•				•					•				
AAT		•				•					•				
SWMT		•				•					•				
IDED		•				•					•				
Urine test	•											•			
Cue reactivity	•											•			
Stroop	•											•			
MIDT	•											•			
Resting state	•											•			
ASL	•											•			
AASE		•				•					•		•	•	•
AUDIT		•													•
BDI		•				•					•				
BIS/BAS		•				•					•				
BIS		•				•					•				
UPPS		•				•					•				
STAI/STATE		•				•					•				
PANAS		•				•					•				
Side effects			•	•	•	•	•	•	•	•	•				
Alcohol use study		•	•	•	•	•	•	•	•	•	•				

##### Neuroimaging study part

The outcome measures concerning brain functioning will be obtained in the week before the first stimulation session (i.e. to measure baseline brain functioning) and in the week after the last stimulation session (i.e. to measure the effect of HF-rTMS). Before the participants enter the scanner they perform a urine alcohol and drug screening and practice the tasks that will be conducted in the MRI scanner.

### Outcomes and instruments

#### Sample characteristics

General patient characteristics such as age, handedness, educational level and use of medication will be assessed. Furthermore the digit span of the Wechsler Adult Intelligence Scale (WAIS) will be used to determine working memory capacity [26]. In addition the Dutch Version of the Adult Reading Test (NLV) will be used to assess premorbid intellectual functioning [27]. The Mini International Neuropsychiatric Interview (MINI) [28] will be used to determine whether the participant has any psychiatric DSM-IV diagnoses. The substance use during life questionnaire from the measurement in the addictions for triage and evaluation (MATE) [29] will be used to assess lifetime drug use. For a comprehensive assessment of the alcohol use history an adapted version of the life time drinking history [30] will be used.

#### Primary outcome measure

The primary outcome of the study will be the abstinence rate after the add-on HF-rTMS treatment (in line with the guidelines of the European Medicines Agency [31]). This will be defined as the number of abstinent days in the 180 days after the last stimulation session measured using the Time Line Follow Back (TLFB) [32] at six months follow up.

#### Secondary outcome measures

The secondary outcome measures of the study will be described below.Total alcohol consumption after the add-on HF-rTMS treatment. This amount (g) of alcohol will be calculated using the TLFB at three months and six months follow-up.Days until the first relapse after the add-on HF-rTMS treatment, wherein relapse is defined as a heavy drinking day. This holds more than 60 g alcohol per day for men and more than 40 g alcohol per day for women [31, 33]. This measure will be assessed using the TLFB at three months follow up and six months follow-up. Individuals who do not relapse will receive the highest score of 90 days.Change in craving levels after the add-on HF-rTMS treatment will be measured using the Alcohol Urge Questionnaire (AUQ) [34] assessed after the last session of the add-on HF-rTMS treatment, at three and six months follow-up.

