## Background

Substance dependence is characterized by drug seeking and drug use which persists despite negative social and health consequences [1]. In the Netherlands approximately 4–5% of the population is suffering from an alcohol use disorder [2]. In 2014 more than 30.000 individuals were registered at addiction treatment centers in the Netherlands with alcohol as primary substance of abuse [3]. Currently only psychosocial and pharmacological treatments are available for alcohol use disorders. However, these treatments are only moderately effective and more than 50% of all treated patients relapses within one year [4]. In an attempt to improve the treatment of substance dependence, non-invasive neuromodulation has gained attention as a new potential treatment option [5, 6].

High-frequency (HF) repetitive transcranial magnetic stimulation (rTMS) [7] is one of several types of neuromodulation techniques. With this method, a magnetic field penetrates through the skull which can inhibit or activate neurons in the cortex. This magnetic field originates from a coil wherein an alternating electric current is running. The alternating current induces high intensity magnetic pulses that pass the skull and generate an electric current in the neural tissue. By using this technique the activity of the targeted cortical area is manipulated [5, 8]. HF-rTMS became a popular investigational treatment tool for several psychiatric disorders because of its non-invasiveness, tolerability and safety [9].

Individuals suffering from alcohol dependence often experience an intense and abnormal desire for alcohol, also known as craving [10]. Furthermore it is known that alcohol dependent individuals show impaired executive functions, such as diminished cognitive control, cognitive flexibility and working memory [11, 12]. It is believed that perceived craving combined with reduced cognitive control leads to problems in managing craving and consequently relapse [1].

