
### Statistical analyses

#### Power analysis

The current study is the first to investigate the effect of multiple HF-rTMS sessions on abstinence rates measured six months after the last stimulation session. To the best of our knowledge no studies thus far have investigated the effect of rTMS on abstinence after a longer - clinically more relevant - period of time. Therefore no effect size is known or can be calculated, which makes it impossible to perform a scientifically correct power analysis. However, to estimate how many participants we would need, we based our population estimate on a previous study with a similar design [20], which used craving as the outcome of interest. Although our secondary outcome measure is craving, we hypothesized that we should at least include a similar number of participants (30 participants in the active stimulation group) as [20]. Given a drop-out percentage of 10%, and an estimated lower effect on behavioral measures compared to craving, the current study will include 38–40 alcohol dependent individuals per group, resulting in a total of approximately 80 participants.

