#### Secondary outcome measures

An appropriate test for comparison of two groups will be used depending on the distribution of the outcome measures ‘days until first relapse’ and ‘total alcohol consumption’.

Multilevel models (capable of handling missing data points) with predictors time, treatment and time X treatment interaction will be used to test for the effect of the HF-rTMS add-on treatment on craving. The following time points will be included: post HF-rTMS, 3 months follow up and 6 months follow up.

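### The 90-day score for participants who do not relapse contradicts the six-month window of the secondary outcome days until first relapse

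*Protocol article*

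**What the plan says.** Under Outcomes and instruments, Secondary outcome measures, the article defines the outcome as "Days until the first relapse after the add-on HF-rTMS treatment, wherein relapse is defined as a heavy drinking day". On timing it states: "This measure will be assessed using the TLFB at three months follow up and six months follow-up". The scoring rule follows directly: "Individuals who do not relapse will receive the highest score of 90 days".

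The Primary outcome measure section fixes the length of the six-month window, because there the outcome is "the number of abstinent days in the 180 days after the last stimulation session measured using the Time Line Follow Back (TLFB"), taken at the six-month follow-up. The Overview of study confirms the contacts: "After three, six and 12 m a 30-min telephone follow-up interview will be held".

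Under Statistical analyses, Secondary outcome measures, the analysis of this outcome and of total consumption is given as: "An appropriate test for comparison of two groups will be used depending on the distribution of the outcome measures". No test is named.

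**The concern.** A count of days observed up to day 180 can take values up to 180, so 90 cannot be its highest value. Ninety days fits a three-month outcome, but the article names both assessments and gives one maximum for both. It does not limit the outcome to the first 90 days, does not say that later relapses are capped, and does not set a separate maximum for six months.

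The 90 is a value assigned to every participant who never relapses, and in most plausible scenarios that is a large share of the sample. It therefore has a strong influence on any comparison made on the score. The outcome answers one of the article's named secondary research questions. With the rule unsettled, the analyst would have to choose between 90, a cap at 90 and 180 once the data are in, and that choice could then depend on the results.

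**Working it through.** **Consistency of the score range.** The largest possible day count equals the length of the window. Three months gives about 90, which matches the stated maximum. Six months gives 180, which does not.

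**Scores under each reading**

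| Course | Literal | Everyone capped at 90 | Non-relapsers scored 180 |
|---|---|---|---|
| Relapse on day 60 | 60 | 60 | 60 |
| Relapse on day 91 | 91 | 90 | 91 |
| Relapse on day 120 | 120 | 90 | 120 |
| No relapse by day 180 | 90 | 90 | 180 |

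Only the last column uses the whole window and keeps non-relapsers at the top. Up to this point no assumption is needed.

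**Illustration of size: inputs**
- 36 per arm, which equals 40 × (1 − 0.10). The Power analysis section plans 38–40 per group and allows 10% drop-out.
- Assumed, not in the article: exponential relapse times, a hazard ratio of 0.5, and sham relapse by day 180 of p = 30, 50 or 70%.
- For context, the Background section says only that "more than 50% of all treated patients relapses within one year". Under a constant hazard, exactly 50% in a year means 1 − 0.5^(180/365) = 29% by day 180, so the 30% scenario sits near that floor.

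**Formulas.** The sham hazard is λ = −ln(1 − p)/180 and the active hazard is λ/2. S(t) = exp(−λt) is the proportion relapse-free at day t, and RM(T) = (1 − exp(−λT))/λ is the mean relapse-free time up to day T. The mean score is:
- literal: RM(180) − 90 × S(180)
- capped at 90: RM(90)
- non-relapsers scored 180: RM(180)

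**Worked case, p = 50%.** λ = 0.003851.
- Sham: S(90) = 0.707, S(180) = 0.500, RM(180) = 129.8, RM(90) = 76.1, literal mean = 129.8 − 45.0 = 84.8.
- Active: S(180) = 0.707, RM(180) = 152.1, RM(90) = 82.6, literal mean = 152.1 − 63.6 = 88.5.
- Active minus sham: 3.6 days literal, 6.6 capped, 22.3 with 180.

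The literal difference equals the 180-day difference less 90 × (active S(180) − sham S(180)): 22.28 − 90 × 0.2071 = 3.64. Each extra non-relapser in the active arm gives up 90 days of credit.

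**All scenarios** (sham relapse by day 180 of 30 / 50 / 70%)

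| Quantity | Literal | Capped at 90 | Scored 180 |
|---|---|---|---|
| Mean difference, days | 1.2 / 3.6 / 8.3 | 3.7 / 6.6 / 10.1 | 13.5 / 22.3 / 30.6 |
| Rank-test power, % | 5 / 8 / 14 | 16 / 28 / 40 | 28 / 45 / 57 |

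The means are exact. The powers are simulated (Mann-Whitney, two-sided 5%), and repeat runs moved them by up to two percentage points. A log-rank test to day 180 gave about 28/44/61%. The share of sham participants with a first relapse on days 91 to 180, S(90) − S(180), is 14/21/25%. Those are the participants whom the literal score places above every non-relapser.

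**The case against.** The strongest counter-argument is the phrase highest score itself. Taken at its word, nothing exceeds 90, so a relapse on day 120 also scores 90. It then ties with no relapse, and nothing is reversed. This stands as a possible reading, so reversed ranking should not be stated as certain. It does not rescue the rule. The cap is not written down, and with it the six-month assessment that the same paragraph names contributes nothing to this outcome. Power also stays well below that of the 180-day score.

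Four further inferences are tempting and not supported.

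- **That an ordinary two-group test will treat censored times as observed.** The analysis section names no test, and a log-rank test also compares two groups. An article may leave that choice to an analysis plan that is not shown. What can be criticised is the assigned value.
- **That group means would point the wrong way.** In every scenario above the difference shrinks but stays positive. A change of sign on the literal reading would need an effect concentrated after day 90, and the article gives no basis for assuming one.
- **That participants reached at three months and then lost cannot be used.** Anyone who relapsed before the three-month interview has a complete value. Only those still relapse-free at that point and then lost are affected.
- **That only a time-to-event model will do.** Changing 90 to 180 recovers nearly all of the power (28/45/57% against 28/44/61%). The time-to-event analysis is preferable, chiefly for those lost early, but the contradiction can be removed without it.

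**Conclusion.** The scoring rule is wrong as written. A 90-day maximum cannot belong to an outcome assessed to 180 days, and nothing in the article reconciles the two. This conclusion comes from the text alone.

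The consequence depends on the reading. Late relapses either outrank never relapsing (literal) or tie with it (cap), and both lose information. In the middle scenario, rank-test power is about 8% or 28% respectively, against 45% with non-relapsers scored 180. These sizes rest on exponential times, a hazard ratio of 0.5 and relapse rates that the article does not give, so they show an order of magnitude and are no forecast. Even correctly scored, the outcome has modest power at this sample size.

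The scope is one secondary outcome. The primary outcome, abstinent days out of 180, does not use this rule and is unaffected.

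**What to change.** Settle the rule before outcomes are compared between arms, in one of these ways:

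- **Minimum:** for the six-month outcome, replace 90 by 180 as the value for participants without a relapse.
- **Preferred:** define the outcome as time to the first heavy drinking day over 180 days. Censor relapse-free participants at day 180, or at the last day covered by the TLFB if they are lost earlier. Name a time-to-event comparison in the analysis section.
- **If a 90-day outcome is intended:** say that it is limited to the first 90 days and that later relapses count as relapse-free at day 90. Remove the six-month assessment from this outcome, or define a separate 180-day version with its own maximum.

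The cost is one sentence in the outcome definition and, for the preferred option, one in the analysis section. No new data are needed, because the three- and six-month interviews already cover the period.

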#### Additional clinical outcome measures

##### Explorative alcohol use parameters

The effect of HF-rTMS on alcohol consumption or abstinence will be assessed using the following explorative outcome measures.Full abstinence rate after the add- on HF-rTMS treatment, defined as the number of participants who did not consume any alcohol after the HF-rTMS treatment. This will be assessed using the TLFB at six months follow-up.Treatment success based on drinking status at 12 m follow up. The drinking status will be subdivided into the following categories: abstinence (defined as no use of alcohol), non-excessive drinking (defined as 21 drinking days per 30 days, with a maximum of 4 glasses per day) and excessive drinking (more than 21 drinking days per 30 days and more than 4 glasses per day) [4]. Participants will be assigned to one of the categories based on the last 30 days of the 12 m follow up TLFB assessment. The categories abstinence and non-excessive drinking will be defined as successful treatment.

##### Additional craving assessment

The effect of HF-rTMS on craving will also be assessed using the short (5-item) version of the Obsessive Compulsive Drinking Scale (OCDS) [35]. This questionnaire will be assessed prior to the first, and after the fifth and tenth stimulation session and at the 3, 6 and 12 months follow-up.

To assess the acute effect of HF-rTMS on craving two 100 mm visual analogue scale (VAS) ranging for 0 (not at all) to 100 (very much) will be assessed prior and after every stimulation session. Participants will be asked to indicate (1) their current desire to consume alcohol: “How much do you feel like drinking alcohol right now?” and (2) their current urge to drink alcohol: “How strong is your urge to drink alcohol right now?” by drawing a line on a VAS scale.

##### Questionnaires

Questionnaires that will be filled in during the study are:Alcohol consumption burden measured with the Alcohol Use Disorders Identification Test (AUDIT) [36].Confidence in abstaining from drinking as measured with the Alcohol Abstinence Self Efficacy (AASE) [37].Depressive symptoms as measured with The Beck Depression Inventory (BDI) [38].Impulsive behavior will be assessed using Barratt Impulsivity Scale-11 (BIS) [39], UPPS (urgency, premeditation, perseverance, sensation seeking) [40] and Behavioral inhibition and Behavioral Activation systems (BIS/BAS) [41] questionnaires.Current state anxiety as measured with the state trait anxiety inventory (STAI STATE) [42].Experience of positive and/ or negative affect measured with the Positive And Negative Affect Scale (PANAS) [43].

##### Supplementary measures

In order to get an overview of the drinking behavior during the testing period (variable defined as: alcohol use study) participants are asked before every HF-rTMS session “whether (1) he/she consumed alcohol in the last 24 hours and if so (2) what kind of alcohol, (3) the alcohol percentage and (4) the amount consumed”. Furthermore participants are asked whether they were suffering from any side effects after the previous HF-rTMS session. The reported side effects will be listed.

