### Intervention

The intervention exists of 10 HF-rTMS sessions of the right DLPFC (rDLPFC) on 10 consecutive workdays. The HF-rTMS parameters of the active intervention are 60 10 Hz trains of five seconds at 110% of the motor threshold [23]. The coil will be oriented over the rDLPFC with a horizontal angle of 45° relative to the nasion-inion midline [24]. For the sham stimulation the stimulator will be set at the same settings, but the coil will be tilted 90° relative to the skull [23]. The rDLPFC will be located at position F4 using the International 10–20 EEG system [25]. During the stimulation participants are situated on a comfortable chair with extra neck support. All sessions are applied at the Jellinek addiction treatment centre in Amsterdam. One stimulation session takes approximately 20–30 min.

The motor threshold will be determined at rest before the first and sixth stimulation session, using single pulse TMS in combination with Motor Evoked Potentials. The muscular (left abductor pollicis brevis) response will be measured by visually observing a thumb muscular abduction. Stimulus intensity will be adjusted until there is an abduction in five out of ten trials. For the rTMS sessions we will use a 70 mm double air film coil (Magstim Co., UK) and a Magstim Rapid^2^ stimulator (Magstim Co., UK). The intervention will be applied by an rTMS trained researcher. The training exists of brain stimulation courses, practical rTMS tutorials, hands on training and first aid and emergency response training. During the stimulation session a predefined protocol will be executed.

The HF-rTMS intervention will be added to the treatment as usual (TAU) provided by the Jellinek addiction treatment centre. This treatment consists of an intensive 3–5 days per week program with group sessions of cognitive behavioural therapy (CBT), emotion regulation training, and motivational enhancement therapy. Besides these sessions, every participant has individual sessions with a psychologist and a mentor every week. In the session with the psychologist, comorbidities and other problems of the patients that occur during treatment are discussed. During the mentor session supportive CBT focussing on remaining abstinent is given. Finally, some patients receive pharmacotherapy.

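### The 24-hour alcohol question, asked only on workdays, leaves about 48 hours of each weekend in the stimulation course unrecorded (minor)

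*Protocol article*

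**What the plan says.** The Intervention section of the protocol article specifies "10 HF-rTMS sessions of the right DLPFC (rDLPFC) on 10 consecutive workdays".

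The Supplementary measures section (under Outcomes and instruments) gives the aim of the variable named alcohol use study: "In order to get an overview of the drinking behavior during the testing period". It then says when the question is put, "participants are asked before every HF-rTMS session", and what it covers: whether "he/she consumed alcohol in the last 24 hours and if so" the kind of drink, its strength and the amount. The side-effects question in the same section is anchored differently: it refers back to the previous session.

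Table 1 schedules alcohol use study on test days 1 to 10 and on no other day. The Supplementary measures section under Statistical analyses plans to compare these measures between the groups.

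Three other entries bear on alcohol consumption:

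- The Time Line Follow Back (TLFB) is taken at three, six and twelve months. The primary outcome derived from it is "the number of abstinent days in the 180 days after the last stimulation session".
- The urine test belongs to the neuroimaging part: "Before the participants enter the scanner they perform a urine alcohol and drug screening". Table 1 places it in the week before the first session and the week after the last, and only a subset of participants is scanned.
- The AUDIT is scheduled on test day 1 and at twelve months.

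**The concern.** The recall window and the asking schedule do not fit together. A 24-hour look-back covers the time between sessions only when sessions are 24 hours apart. Between a Friday and a Monday session there are about 72 hours, and the Monday question reaches back over only the last 24.

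The aim is an overview of the testing period, and the sample is enrolled as abstinent. The item is the only planned record, for the whole sample, of whether abstinence held while stimulation was being given. If some of that time is never asked about, a participant can answer every question truthfully and still have drunk during the course without trace. The recorded level of in-treatment drinking would then be too low, and the variable that enters the group comparison would not be the one the article describes.

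**Working it through.** The article states no figure for coverage, so there is none to reproduce. The check is a calendar count.

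**Inputs from the article.** Ten sessions on consecutive workdays (Intervention); the question put before each session with a 24-hour look-back (Supplementary measures); no administration outside test days 1 to 10 (Table 1).

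**Assumptions.** Workdays are Monday to Friday, no public holiday falls in the course, and sessions are at the same clock time each day. The article does not give the weekday of session 1, so every start day is counted.

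**Time covered.** Between session 1 and session 10, the questions at sessions 2 to 10 apply: 9 × 24 h = 216 h. The question at session 1 looks back before the course begins and is left out.

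**Time elapsed.**

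| Start day | Last session | Weekends inside | Elapsed | Covered | Unasked | Share |
|---|---|---|---|---|---|---|
| Monday | Friday of week 2 | 1 | 11 × 24 = 264 h | 216 h | 48 h | 48/264 = 18.2% |
| Tuesday to Friday | Monday to Thursday of week 3 | 2 | 13 × 24 = 312 h | 216 h | 96 h | 96/312 = 30.8% |

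Each weekend therefore contributes 72 − 24 = 48 unasked hours, from the Friday session to the same clock time on Sunday.

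**Sensitivity to session time.** With the Friday session at hour f and the Monday session at hour m, the gap is 48 + m − f. For session times between 09:00 and 17:00 it runs from 48 + 9 − 17 = 40 h to 48 + 17 − 9 = 56 h.

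**Sensitivity to the base.** If the 24 hours before session 1 are included, a Monday start leaves 2 of 12 days unasked (17%) and any other start 4 of 14 (29%). The gap per weekend is the same; only the denominator moves.

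**Does another measure fill the gap?** The TLFB outcomes count from after the last session. The urine test falls before and after the course, and only in the scanned subset. The AUDIT is not repeated within the course. The visual analogue scales, AUQ and OCDS measure craving, not consumption. None of them records drinking on a weekend inside the course.

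**After the change.** A window reaching back to the previous session covers 264 of 264 h or 312 of 312 h, a gap of 0 h.

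**The case against.** The strongest reply is that the variable is supplementary, sits beside side effects, and is meant only to give an overview. No analysis in the article uses it to adjust, censor, exclude or define treatment completers. That stands, and it limits the severity. It does not remove the mismatch: the article states the window and the aim explicitly and plans a group comparison of the result. The phrase testing period could be read as the test days alone, but a continuous period is the more natural reading. Condensation into an article does not explain the gap either, because the window is stated, not omitted.

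Several stronger readings are tempting, and the article does not support them:

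- A reader might infer that the whole weekend is lost. It is not. Monday's question captures drinking from Sunday, at the session's clock time, onward.
- A reader might infer that the gap distorts days until first relapse or the primary outcome. Both are defined from after the stimulation course, so drinking within it lies outside them whether or not it is recorded.
- A reader might infer that the missed hours are those when drinking is most likely. The article gives no drinking by day of the week, and usual treatment runs three to five days a week, so some weekdays may also be free of the programme.
- A reader might infer bias in favour of one arm. Both arms get the same question on the same schedule, and nothing in the article points to differential error.
- A reader might infer that anyone who drinks on a Saturday is classed as abstinent in treatment. The lapse is missed only if it stays within the unasked hours, and the article does not turn negative answers into such a class.

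**Conclusion.** The point holds as a minor one. As written, the item does not record drinking from each Friday session until 24 hours before the Monday session: about 48 hours per weekend, or 18% of the time between sessions 1 and 10 for a Monday start and 31% for other start days. These figures rest on Monday-to-Friday workdays, no holidays and a constant session time; varying the time between 09:00 and 17:00 gives 40 to 56 hours per weekend.

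The consequence is under-counting of in-treatment drinking in both arms, possible attenuation of the planned comparison of this one variable, and possible loss of lapses confined to those hours. How much drinking is missed cannot be worked out from the article. The primary and secondary outcomes are unaffected.

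**What to change.** Change the recall window from the last 24 hours to the time since the previous session, and keep 24 hours at session 1, where there is no previous session. Record kind, strength and amount separately for each day in the window, so that Monday's answer gives Friday after the session, Saturday, Sunday and Monday up to the session. The side-effects question already uses the previous session as its anchor, so the two items would then match.

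The cost is slightly longer questioning on Mondays and a recall of about three days instead of one. If data have already been collected with the present wording, describe the variable in the report as drinking in the 24 hours before each session and state the weekend gap.

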##### Supplementary measures

These measures will be compared between groups using an appropriate statistical test depending on the distribution of the outcome measure.

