If this study reveals higher abstinence rates and decreased craving in the active stimulation group compared with the sham stimulation group, and the active HF-rTMS induces negligible side effects, this may lead to larger clinical trials. If most of these trials find positive results of multiple HF-rTMS sessions on treatment outcomes, this eventually could result in approval by the regulatory authorities as additional treatment method for substance dependence, just as for instance the Food and Drug Administration has approved HF-rTMS for the treatment of depression.

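### The scheduled side-effect question never covers the last session a participant receives, so the side-effect listing can only undercount

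*Protocol article*

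**What the plan says.** Under Outcomes and instruments, the Supplementary measures paragraph describes two enquiries. For alcohol use, "participants are asked before every HF-rTMS session" about the preceding 24 hours. It then adds that "participants are asked whether they were suffering from any side effects after the previous HF-rTMS session", and that what is reported will be listed.

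Table 1 gives the timetable. The Side effects row is marked on test days 2, 3, 4, 5, 6, 7, 8, 9 and 10. It is blank on day 1, in the week after the last session (column XX), and at three, six and twelve months. The row below it, for alcohol use during the study, is marked on all of days 1 to 10.

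The Intervention section sets "10 HF-rTMS sessions of the right DLPFC (rDLPFC) on 10 consecutive workdays". Later contacts do exist: the post-treatment MR visit for the neuroimaging subset and, from Overview of study, "After three, six and 12 m a 30-min telephone follow-up interview will be held".

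Two uses of the data are stated. In the Supplementary measures paragraph of the statistical section, "These measures will be compared between groups using an appropriate statistical test". The Discussion says that if abstinence and craving improve and "the active HF-rTMS induces negligible side effects, this may lead to larger clinical trials".

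**The concern.** A question that looks back one session needs one more asking than the schedule provides. Asked on day 10, it covers session 9, and nothing in Table 1 then covers session 10. The same holds for anyone who leaves treatment early and does not return: the question about their last session would have been put at a visit they never attended.

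The gap is modest in volume, but it does not fall at random. For a participant who leaves, the uncovered session is the one immediately before leaving, which is where a new effect that prompted the departure would sit. A listing built this way can fall short of the true number of affected participants but cannot exceed it on this account. The trial's tolerability statement, both the comparison between arms and the Discussion's remark about negligible side effects, rests on that listing as far as the article describes it.

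**Working it through.** The plan states no figure for side-effect coverage, so there is none to reproduce. The check is a count of sessions against enquiries.

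**Inputs**
- Sessions per completer: 10 (Intervention).
- Scheduled side-effect enquiries: 9, on test days 2 to 10 (Table 1).
- Participants: "the current study will include 38–40 alcohol dependent individuals per group, resulting in a total of approximately 80 participants" (Power analysis); 80 is used here.
- Drop-out: 10% (Power analysis). The article does not say whether this occurs during stimulation or during follow-up.
- MRI subset: 28 per group (Power analysis, Neuroimaging study part).

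**Which session does each mark cover?** The text refers to the previous session. The blank on day 1, where the alcohol row has a mark, fits a question with nothing yet to look back on. So the mark on day k+1 covers session k, and the day 10 mark covers session 9.

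**Completers.** Covered sessions = 10 − 1 = 9, so 1 of 10 is uncovered. If all 80 complete: 80 × 10 = 800 sessions, 80 × 9 = 720 covered, 80 uncovered (10.0%).

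**Early stoppers who do not return.** With k sessions received, the covered share is (k − 1)/k:

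| Last session received | Covered share |
|---|---|
| 1 | 0% |
| 3 | 67% |
| 5 | 80% |
| 9 | 89% |

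**Whole trial, with assumed withdrawal during stimulation.** Suppose q of 80 stop after session k and none returns. Sessions delivered = (80 − q) × 10 + q × k, and uncovered sessions = 80.
- q = 8 (10%), k = 1: 72 × 10 + 8 = 728, and 80/728 = 11.0%.
- q = 8, k = 9: 720 + 72 = 792, and 80/792 = 10.1%.
- Over withdrawal of 5% to 20% and k from 1 to 9, the share runs from 10.1% to 12.2%.

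**Effect on the proportion of completers with any side effect (illustration).** The article gives no event rates. Assume a constant, independent risk r per session. The true proportion is 1 − (1 − r)^10 and the proportion that the nine enquiries can show is 1 − (1 − r)^9:

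| Assumed r | Any effect in 10 sessions | Any effect in the 9 covered |
|---|---|---|
| 0.02 | 0.183 | 0.166 |
| 0.05 | 0.401 | 0.370 |
| 0.10 | 0.651 | 0.613 |

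Under these assumptions the shortfall is about 2 to 4 percentage points.

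**After the change.** One enquiry after the last session received raises coverage to 10/10 for completers and k/k for early stoppers. Uncovered sessions fall from 80 to 0 if everyone is reached.

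**The case against.** The strongest reply is that this is one supplementary question in a condensed article. Adverse-event reporting and withdrawal procedures commonly sit in the full protocol, which is not shown. Participants also remain in contact with the centre: day 10 includes assessments after stimulation, and usual treatment continues with weekly individual sessions. This stands as a limit. Not covered here means not covered by the scheduled question, and spontaneous reports or other procedures may catch some events. It does not remove the point, because the wording and the visit-by-visit schedule are both given, they agree, and together they leave the last session out.

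A reader might go further and infer that side effects causing withdrawal are never recorded. The article does not support that. The question is linked to the pre-session enquiries, so a participant who comes to the next visit, reports an effect and then declines stimulation has been asked. An effect that began earlier and persisted would have been asked about at the preceding visits. Only an effect first arising after the last session, in someone with no later side-effect enquiry, escapes.

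A reader might also infer that about four participants per arm will stop treatment and go unrecorded. The phrase "Given a drop-out percentage of 10" per cent is not tied to the stimulation phase, and the loss that the Discussion treats as the main challenge is loss to follow-up.

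Finally, one might expect the undercount to fall mainly on the active arm and so flatter it. That is conceivable, but no side-effect or withdrawal rates are given for either arm. The rule itself omits one session per participant in both arms alike, with no built-in imbalance.

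It is also fair to say that the Discussion's remark is not a formal decision rule, and that no primary or secondary outcome depends on these data.

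**Conclusion.** The point holds as a gap in a stated collection schedule. Session 10 has no scheduled side-effect enquiry in completers (1 of 10 sessions each; 80 of 800 if all 80 complete), and a participant who leaves without returning is not asked about the last session received. With assumed withdrawal of 5% to 20% during stimulation, the uncovered share of delivered sessions is 10.1% to 12.2%.

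The direction for the scheduled listing is certain: it can only undercount. The size and direction of any distortion between arms cannot be derived from the article. The conclusion rests on reading the day k+1 mark as covering session k, which both the text and the day 1 blank support. The count of one uncovered session per participant further assumes that early stoppers do not come back for another visit; each one who does reduces it.

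The primary and secondary outcomes are untouched. The change is still worth making, because the tolerability comparison draws on these data and the repair is very small.

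**What to change.** Keep the pre-session question as it is, and add:

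- an enquiry at the end of test day 10 for immediate effects of session 10, when participants are still present for the post-stimulation assessments;
- the same question within days of session 10, at the MR visit for those who have one and by a short call for the others;
- for anyone who discontinues early, the same question about the last session received, together with the reason for stopping, by a call within days.

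Add the matching marks to the Side effects row of Table 1, and report side effects leading to discontinuation by arm.

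Cost: the MR visit serves 2 × 28 = 56 participants, so about 80 − 56 = 24 need a short call, plus any early stoppers. Waiting for the three-month interview would avoid the calls but would rely on weaker recall, so it should serve only as a back-up. No existing measure or analysis has to change.
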